#### Balance and mobility

The Four Square Step Test (FSST) requires subjects to rapidly change direction while stepping forward, backward, and sideway, over a low obstacle. Time to complete the test is measured. The test has been validated in older adults [63] with sensitivity of 85% and specificity of 88-100% in predicting fall risk [63].

The Short Physical Performance Battery (SPPB) consists of three types of physical maneuvers: the balance tests, the gait speed test, and the chair stand test. The SPPB is highly reliable in older adults (ICC=0.83-0.89) and has demonstrated a strong and consistent association with health status measures, in spite of the socioeconomic and cultural differences [64].

The mini-Balance Evaluation Systems Test (mini-BESTest) is a performance based measure differentiating balance problems into 6 underlying systems that may be impaired: biomechanical, stability limits, postural responses, anticipatory postural adjustments, sensory orientation, dynamic balance during gait and cognitive effects. The mini-BESTest has been shown to be a reliable (ICC=0.91) and valid measure of balance in individuals with PD [65].

Community ambulation will be assessed using 1) the Physical Activity Scale for the Elderly (PASE). This 27 item self report questionnaire assess habitual physical activity in the home and community environment. The questionnaire was designed to address cultural differences, is available in multiple languages and has been validated for older adults [66]; 2) a tri-axial accelerometer (Axivity Ltd.) will be worn by the participants for 7 days to quantify and monitor stepping and physical activity. The device which records at 100Hz will be mounted on the trunk (L5) and will derive the following outcome measures: step count, postural transitions, sedentary time, percentage walking time, number and time of walking and sedentary bouts. Data will be obtained one-week pre and post training.

#### Cognitive function

Cognitive function will be assessed using a computerized neuropsychological test battery (Mindstreams®, NeuroTrax Corp., NJ) [67]. The battery assesses different cognitive domains including memory, attemtion, executive function, visual spatial processing and a global cognitive composite. The test battery generates age and education adjusted composite indices of each cognitive domain on an IQ like scale, with the score of 100 representing the estimated population mean normalized for age and education level. The battery has been validated in elderly adults, patients with mild cognitive impairment, and patients with PD and has shown to be useful in predicting falls [17,21,68-70].

In addition, we will also include standardized neuropsychological tests such as the Montreal Cognitive Assessment (MoCA); a rapid screening instrument for global cognitive dysfunction. Different cognitive domains are assessed (attention and concentration, executive functions, memory, language, visuo-constructional skills, conceptual thinking, calculations, and orientation). The MOCA was found to be a valid instrument for cognitive screening in MCI and PD [71,72]. In this study the MoCA will be used as a descriptive measure.

The Trail Making Test (TMT) is a neuropsychological test of visual attention and task switching. It consists of two parts in which the subject is instructed to connect a set of 25 dots as fast as possible while still maintaining accuracy. The test provides information about visual search speed, scanning, speed of processing, mental flexibility, and executive functioning. The TMT is valid and reliable for older adults [73,74] and has been previously associated with decreased gait speed, dual task activity, and obstacle clearance [75].This is a well suited outcome measure given the nature of the training.

Verbal Fluency is a test of working memory and language in which participants have to say as many words as possible from a category in a given time (usually 60 seconds). The test includes both semantic and phonemic sections, is related to executive function, and has been shown to be highly reliable and valid in the elderly population [76].

#### Health-related quality of life

The SF-36 Health Survey is a generic self-report questionnaire designed to address health related quality of life. The SF-36 includes one multi-item scale measuring several constructs such as physical functioning; bodily pain; social functioning; general mental health (psychological distress and psychological wellbeing); vitality (energy/fatigue); and general health perceptions. Criterion validity has been established but the scores could also be divided into two aggregate summary measures; the Physical Component Summary (PCS) and the Mental Component Summary (MCS). SF-36 has been validated for older adults and patients with PD [77,78].

Fear of Falling will be evaluated using the Falls Efficacy Scale-International. The FES-I has been significantly associated with performance-based measures of balance and mobility including gait speed and medial-lateral sway. The scale has been shown to be sensitive to change in older adults with and without cognitive impairments [79,80].

#### User satisfaction and views

A questionnaire was developed by the researchers to assess the satisfaction of the participants from the training and to try and obtain subjective information regarding the usability and efficacy of such an intervention in reducing fear of falling, fall risk and frequency of falls.

### Data analysis

Statistical analysis will be undertaken using SPSS version 19.0 (SPSS Corp, Chicago, IL, USA). All analysis will be conducted on an intention-to-treat principle using all randomized participants. Demographic characteristics and baseline data will be summarized by descriptive statistics using means, standard deviations and 95% confidence intervals for continuous variables, median and inter-quartile ranges for non-normal continuous or ordinal data and percentages for categorical data, and will be evaluated for normalcy and homogeneity. For the primary outcome measure, fall rate will be analyzed by calculating relative risk using negative bionomial regression models that adjust for any potential confounders [81]. Fall rate and fall status (none faller, faller and multiple faller) will then be compared within and between groups. The secondary outcome measures will be analyzed using repeated measures analysis of variance (RMANOVA) to assess differences between groups (intervention) and across time (follow up) for each group of participants and then compared across groups. All data will be adjusted for multiple comparisons.

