**Figure 1 F1:**
[figure not shown]
**The V-TIME multi-modal intervention solution for reducing fall risk.** Current treatment of fall risk focuses on motor, e.g., gait, problems. V-TIME focuses on both gait and cognitive deficits to optimally treat multiple, critical fall risk aspects and enhance mobility, physical activity and cognitive function. The current working version of V-TIME is shown. A patient trains on a treadmill while viewing a virtual environment that presents obstacles, different types of challenges, and feedback [49]. Written informed consent was obtained from the patient for publication of this case report and any accompanying images. A copy of the written consent is available for review by the Editor-in-Chief of this journal.

In a pilot study [49], 20 patients with PD participated in an intervention based on a VR system for an obstacle navigation task. Patients walked on a treadmill while negotiating obstacles in a VR scene projected on a wall in front of them. They trained for 3 times a week for 6 weeks for about 45 minutes in each session. Visual and auditory feedback was provided by the VR simulation upon error or success and at the end of each walk. After 6 weeks of training, comfortable gait speed significantly improved, as did stride length, gait variability, and over-ground obstacle negotiation. Dual task (DT) performance improved and there was evidence of enhanced task planning and set shifting. Increased gait speeds under all conditions (i.e., comfortable, fast, DT and six minute walk) were not only maintained at follow-up, but also continued to improve 4 weeks later, suggesting that the training generated a positive feedback loop that modified behaviour and overall mobility [49]. Encouraged by these results, an additional pilot study was carried out. Five elderly women who sustained at least 2 falls in the 6 months prior to the study trained using the same treadmill training with VR protocol. Here too, after training, improvements were observed in dual tasking, cognitive function, gait, and mobility, but perhaps the most promising finding was a decrease of 73% in the frequency of falls in the 6 months post-training as compared to 6 months pre-training [52].

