The accumulating evidence on the importance of cognitive function to gait and falls combined with these initial findings formed the basis of the present study. The primary aim is to demonstrate that six weeks of treadmill training augmented by VR (TT+VR) reduces the risk of falls in a relatively large and diverse group of older adults (n=300), many of whom will likely have a spectrum of motor and cognitive deficits. The study will compare training effects of TT+VR against an active control paradigm (TT without VR) in a randomized controlled trial. We hypothesize that a 6 week intervention with TT+VR compared to TT alone will reduce the incidence of falls and decrease the risk of falls in elderly adults, patients with PD and individuals with MCI. As a secondary question, we will also explore the neural correlates associated with dual task activation and any plastic effects resulting from the training using imaging techniques. However, protocols for these studies will not be presented in this manuscript.

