## Methods/ Design

### Design

A prospective, single blinded, parallel group, randomized controlled trial (RCT) with 6 month follow-up will be employed. The study will include 300 older participants who have experienced two or more falls in the previous 6 months. Participants will be randomized to either the intervention or control group. The intervention group will receive 18 sessions of Treadmill Training with Virtual Reality (TT+VR) and the active control comparison will receive 18 training sessions of treadmill training alone (TT) without the VR simulation (see Figure 2).

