#### Common inclusion criteria

• 2 or more falls within 6 months prior to the beginning of the study

• Aged 60–85 years

• Able to walk for 5 minutes unassisted

• Adequate hearing (as evaluated by the whisper test) and vision capabilities (as measured using a Snellen chart).

• Stable medication for the past 1 month and anticipated over a period of 6 months

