### Sample size calculation

The primary outcome measure is fall incidence rates during the 6 month post-training follow-up period. The sample size estimate is based on extrapolations from our pilot studies [49] and other related promising pilot work (e.g., Rosenblat et al. [54], Pai et al. [55] and, Weerdesteyn et al. [56]). Power was set at 80%, alpha was set at 5% and we accounted for drop out rate of 20%. Using a relatively conservative estimate, we assume that the control group fall incidence rate, after intervention, will be three falls per year. If we consider a 40% reduction for the treatment group relative to this, then, during the 6 month monitoring of falls incidence, a total of 166 subjects would be required for 80% power (83 in each group) to detect differences between the two treatment groups assuming non-inferiority with moderate correlations among covariates (R-squared = 0.50). A much smaller sample is needed to detect between group differences for the secondary outcomes. For example, with 22 subjects in the intervention and control arms, we will have 90% power to detect an intervention effect (assuming Cohen’s f for ANOVA of 0.21), in dual tasking gait speed. To enhance our ability to examine the effects of the intervention on fall incidence within the three sub-groups (seniors, PD, MCI), we will aim to recruit 100 subjects per group, for a total of 300 subjects.

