### Outcome measures

#### Primary outcome measures

The primary outcome measure of the study is fall rate. Participants will keep a falls calendar for 6 months post intervention. Consistent with the recommendations of the Prevention of Falls Network Europe (ProFaNE), a fall will be defined as “an unexpected event in which the participant comes to rest on the ground, floor or lower level”. Each time the participant falls he/she will tick the date on the calendar. These calendars will be returned to the researchers every two weeks in a pre-addressed envelope or using an online electronic calendar. Periodic contact by the research staff with each participant will be used to maximize compliance with the fall calendars.

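### Entry requires two or more recent falls, so a before-after comparison of falls within an arm, the likeliest meaning of the planned within-group comparison, would confuse training with regression to the mean

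*Protocol article*

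**What the plan says.** The hypothesis in the Background is between arms: "We hypothesize that a 6 week intervention with TT+VR compared to TT alone will reduce the incidence of falls". The primary analysis in Data analysis fits it: "fall rate will be analyzed by calculating relative risk using negative bionomial regression models that adjust for any potential confounders". The next sentence adds a further comparison: "Fall rate and fall status (none faller, faller and multiple faller) will then be compared within and between groups".

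Entry is selected on the outcome itself. The Common inclusion criteria require "2 or more falls within 6 months prior to the beginning of the study", and the Design section repeats it: "The study will include 300 older participants who have experienced two or more falls in the previous 6 months". Post-training falls are then counted over a window of the same length: "Participants will keep a falls calendar for 6 months post intervention". Table 1 marks fall frequency at the six-month visit only.

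Two other places bear on the point. The Sample size calculation states that "we assume that the control group fall incidence rate, after intervention, will be three falls per year" and assumes a 40% reduction against that rate. The Background describes as its most promising pilot result "a decrease of 73% in the frequency of falls in the 6 months post-training as compared to 6 months pre-training", in five women who also had at least two falls in the 6 months before that study.

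**The concern.** Comparing an arm with itself needs two periods. The calendar supplies only the period after training, so the evident comparator is the fall history that qualified the person for entry. The pilot used falls in this way. People chosen because they recently fell at least twice are, on average, caught in a bad spell, and their next 6 months will tend to look better whether or not training works.

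This affects what the trial may conclude. The Abstract and Conclusions promise to show how far the intervention lowers fall risk and, separately, what virtual reality adds to treadmill training. There is no untrained arm. A claim that training itself lowers falls, as distinct from the added value of virtual reality, could rest only on before-after change, which cannot separate training from selection. The article gives no caution about regression to the mean.

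**Working it through.** **Plan figures.** The plan gives no figure for a within-group comparison. Its 166 (83 per arm) belongs to the between-arm test. It is approached, for example, by a one-sided 5% Poisson Wald calculation with R-squared 0.50 and no dropout: (1.645 + 0.842)² × (1/1.5 + 1/0.9) / (ln 0.6)² / 0.5 = 84.2 per arm. Nothing below depends on it, except that 83 is used as an arm size.

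**Inputs from the article.** Entry: at least 2 falls in 6 months. Control rate after training: 3 per year = 1.5 per 6 months. Effect: 40%, so 0.9 per 6 months. Annual proportion who fall: about 30% in older adults, 60-80% in PD, MCI or dementia.

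**Assumptions, not in the article.** Each person has a stable personal fall rate and training has no effect. Counts are Poisson given that rate. Personal rates follow a gamma distribution with dispersion k (k = 0 means all alike). A multiple faller has two or more falls.

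**Status.** All participants enter in the worst category, so nobody can worsen. Any change in status is an improvement.

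**Rate, calibrated to the plan's 1.5 per 6 months after entry.**
- Poisson, mean 1.5: P(N≥2) = 1 − 2.5e^(−1.5) = 0.442.
- Mean before training, given entry: 1.5(1 − e^(−1.5)) / 0.442 = 2.635.
- Apparent drop: 1 − 1.5/2.635 = 43%. Still multiple fallers: 44%.
- Gamma-Poisson, k = 1: a 6-month source mean of μ = 0.686 gives a pre-training mean of 2 + μ = 2.686 and a post-training mean of (3 + μ)μ/(1 + μ) = 1.50. Drop: 1 − 1.5/2.686 = 44%.
- For k from 0 to 6: pre-training mean 2.64-2.71, drop 43-45%, 39-44% still multiple fallers, 22-33% with no fall.
- Power of a paired within-arm test exceeds 0.999 with 50 or more per arm.
- In 2,000 simulated no-effect trials at 83 per arm (k from 0.5 to 4), both arms showed a significant reduction in 100% of trials. The between-arm test rejected in 4.9-5.9%.

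**Rate, calibrated to the Background incidences.** The annual mean is m = ((1 − p)^(−k) − 1)/k, or −ln(1 − p) when k = 0, and the 6-month mean is m/2. For p = 0.80 and k = 2: m = (25 − 1)/2 = 12, so 6 per 6 months.

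| Fall in a year | k | 6-month mean | Before | After | Drop with no effect | Still ≥2 falls | Within-arm power, n = 83 |
|---|---|---|---|---|---|---|---|
| 30% | 0 | 0.178 | 2.06 | 0.18 | 91% | 1.5% | 1.00 |
| 30% | 2 | 0.26 | 2.42 | 1.00 | 59% | 25.9% | 1.00 |
| 60% | 0 | 0.458 | 2.16 | 0.46 | 79% | 7.8% | 1.00 |
| 60% | 2 | 1.312 | 3.94 | 3.22 | 18% | 66.8% | 0.77 |
| 80% | 0 | 0.805 | 2.30 | 0.80 | 65% | 19.3% | 1.00 |
| 80% | 2 | 6.0 | 9.87 | 9.57 | 3% | 87.4% | 0.09 |

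**The case against.** The strongest objection is that the article never says before versus after, paired, or within arm. In the same paragraph *group* serves for both arms and patient groups, and the Sample size calculation speaks of intervention effects inside the three patient sub-groups. The sentence could therefore mean arms compared inside each patient group, which would be harmless. The absence of a pre-training mark for falls in Table 1 can also be read as a sign that no before-after analysis is scheduled. This stands as a real ambiguity, and it rules out a fix that simply strikes the within-group comparison: under that reading, the sub-group analysis for which recruitment was raised to 300 would go with it.

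It also stands that the disputed sentence is supplementary. The hypothesis and the primary model are between arms, both arms regress equally, and the simulated between-arm error stays near 5%.

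Three stronger readings are tempting but not supported:
- A reader might infer that a significant fall in rate is guaranteed in each arm. That follows when the post-entry mean is fixed at 1.5, but that figure is an after-training assumption and may already include a treadmill effect. With frequent and very heterogeneous fallers the artefact shrinks to about 3%.
- A reader might set the entry minimum of 2 against the plan's rates and read off drops of at least 25% (1 − 1.5/2) and 55% (1 − 0.9/2) as artefact. Both use assumed post-training rates, and the second contains the assumed 40% treatment effect.
- A reader might infer that pre-training falls come from recall and so are measured differently from calendar falls. The article does not say how entry falls are ascertained.

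**Conclusion.** The point holds as a fault in one supplementary comparison and in what could be concluded from it. If the within-group comparison is before versus after in an arm, it is confounded by regression to the mean, because entry is selected on the outcome. For status the direction is fixed by the entry rule. For rate a drop is expected without any training effect. Its size is about 43-45% if personal rates are stable and the post-entry mean is 1.5 per 6 months, and about 3% to 91% under the Background incidences with k from 0 to 2. The dispersion values are assumptions. The before-after reading is the likelier one but is not stated. The between-arm negative binomial comparison is not biased, so the primary test needs no change. The sentence is still worth correcting, because it governs whether a before-after drop could be presented as an effect of training.

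**What to change.** In Data analysis, define *groups* and state that fall rate and fall status are compared between the randomised arms, overall and within each patient sub-group (older adults, MCI, PD). State that efficacy conclusions rest only on these between-arm comparisons.

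Do not test before-after change in falls within an arm. If pre-training counts are tabulated, present them as descriptive and say beside the table that a reduction is expected from selection on two or more falls. The pre-training fall count may be used as a baseline covariate in the negative binomial model.

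The cost is a sentence or two of text. No data, participants or between-arm power are lost, and the sub-group comparisons remain.

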### Assessment protocol

A repeated measures design will be employed with assessments performed 1 week pre-training, post-training, and at 1 month and 6 months post intervention (Table 1). A trained assessor in each centre, not involved in training and blinded to group allocation, will perform all assessments. Each participant will be assessed at about the same time of day to avoid variability of performance due to any circadian rhythms or medication intake cycle.

**Table 1 T1:** Assessment of outcome measures across the protocol

	**Category**	**Outcome measures**	**Pre training**	**Post training**	**One month follow up**	**Six month follow up**
Primary outcome measure	Falls	Fall frequency				x
Secondary outcome measures	Gait	Gait speed	x	x	x	x
		Gait variability	x	x	x	x
		2 MWT	x	x	x	x
	Balance and mobility	FSST	x	x	x	x
		SPPB	x	x	x	x
		mini-BEST	x	x	x	x
		Community ambulation	x	x	x	
	Cognitive function	MoCA	x			
		TMT	x	x	x	x
		Mindstreams tests of cogntive function	x	x		x
		Verbal Fluency	x	x	x	x
	Healthy Related Quality of Life	SF-36	x	x	x	x
		FES-I	x	x	x	x
	User satisfaction and views	User satisfaction Questionnaire		x		

2MWT- 2 Minute Walk Test, FSST-Four Square Step Test, SPPB- Short Physical Performance Battery, mini-BEST- The mini-Balance Evaluation Systems Test, MOCA- Montreal Cognitive Assessment, TMT- Trail Making Test, FES-I- Fall Efficacy Scale International.

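### Repeated measures ANOVA, as named for the secondary outcomes, cannot by itself use all randomised participants; a mixed model with baseline as covariate should replace it

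*Protocol article*

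**What the plan says.** Three statements in the protocol article bear on this point.

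- **Population** (Data analysis): "All analysis will be conducted on an intention-to-treat principle using all randomized participants".
- **Method** (Data analysis): "The secondary outcome measures will be analyzed using repeated measures analysis of variance (RMANOVA) to assess differences between groups (intervention) and across time". This is done within each participant group and then across groups. The software is fixed ("Statistical analysis will be undertaken using SPSS version 19.0"), but the SPSS procedure is not named.
- **Expected loss** (Sample size calculation): "we accounted for drop out rate of 20" per cent.

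The Assessment protocol section sets four assessments: before training, after training, and 1 and 6 months later. Table 1 shows which outcome is taken when. The article mentions no imputation and no mixed or likelihood-based model for the secondary outcomes.

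**The concern.** Classical repeated measures ANOVA works on complete rows. A participant who lacks one scheduled value of an outcome drops out of the analysis of that outcome, and the values already collected from that person are not used. Under that method, the plan's own drop-out allowance means that the secondary analyses would not include everyone randomised.

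Two things are at stake. First, the participants are repeat fallers aged 60 to 85, some with Parkinson's disease or mild cognitive impairment. If missed visits relate to falls, decline or tolerance of the training, the comparison of arms among completers could be biased. Second, with pre-training as one of the time levels, the baseline value becomes one of the outcomes and is not used as a covariate, which gives up precision that already collected data would provide.

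**Working it through.** **1. The plan's own secondary-outcome figure.** Sample size calculation states: "with 22 subjects in the intervention and control arms, we will have 90% power to detect an intervention effect", for dual tasking gait speed with Cohen's f = 0.21. I read this as 22 per arm, N = 44. The correlation between visits is not stated; I assume ρ = 0.5, with sphericity and α = 0.05. For the group-by-time test with k = 2 arms and m = 4 visits:

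- λ = f²·N·m/(1 − ρ) = 0.0441 × 44 × 4/0.5 = 15.52
- df1 = (k − 1)(m − 1) = 3; df2 = (N − k)(m − 1) = 126
- Power = 0.918, which agrees with the stated 90%.

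The result depends on ρ: 0.794 at ρ = 0.3 and 0.966 at ρ = 0.6. The between-group main effect does not reproduce the figure (0.30 to 0.51 over m = 2 to 4 and ρ = 0.3 to 0.8). The stated power therefore fits a group-by-time test on complete four-visit data.

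**2. The same example under complete-case loss.** 44 × 0.8 = 35.2, so about 35 remain. Then λ = 0.0441 × 35 × 4/0.5 = 12.35, df2 = 99, and power is 0.836. Keeping 44 completers would need 44/0.8 = 55 participants.

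**3. Which outcomes are exposed.** Table 1 lists 14 secondary outcome rows.

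| Outcomes | Scheduled visits | Exposure |
|---|---|---|
| Gait speed, gait variability, 2MWT, FSST, SPPB, mini-BEST, TMT, verbal fluency, SF-36, FES-I (10 rows) | all four | any missed visit removes the person |
| Community ambulation | no 6-month visit | loss after 1 month removes nobody |
| Mindstreams | no 1-month visit | missing 1 month removes nobody |
| MoCA, user satisfaction | once each | not repeated outcomes |

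**4. Size for the ten four-visit outcomes.** If 20% are lost before the last visit, 300 × 0.8 = 240 remain and 60 leave. Per sub-group, 100 × 0.8 = 80 remain and 20 leave.

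**5. Illustration with scattered missed visits.** The documents give no rate for these, so p is an assumption: an independent chance p of missing each of three post-training visits, on top of 20% drop-out. Share complete = 0.8 × (1 − p)³.

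- p = 5%: 0.8 × 0.857 = 0.69, about 69 of 100
- p = 10%: 0.8 × 0.729 = 0.58, about 58 of 100

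**6. Limit of the mixed model.** With baseline as a covariate, it uses anyone with at least one post-training value. If all 60 left during the six training weeks, before any post-training assessment, it would keep the same 240. The later the losses and the more scattered the missed visits, the more it recovers.

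**The case against.** The strongest reply is that the conflict is conditional. The article never says that only completers are analysed; it says the reverse. Imputation before the ANOVA, or a mixed-model fit in the same software, would satisfy both sentences, and missing-data handling is commonly left to the full protocol or analysis plan, neither of which is shown. This stands. A reader might infer that the secondary analyses are completer analyses by design, and the text does not support that. What remains is that the article commits to a named method which, unaided, does not yield the population it states.

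Other stronger readings also fail:

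- **At least 20% lost from every analysis.** The 20% is a planning allowance in the sample size section, not an observed rate or a floor, and Table 1 shows that exposure differs by outcome.
- **Bias as established.** The documents do not say who will miss visits. Complete-case arm contrasts also remain valid if missingness depends only on factors in the model, such as arm.
- **Power as the issue.** The plan's example needs 44 participants, and even 240 completers of 300 far exceed that.
- **Baseline as a time level as an error.** It is a legitimate longitudinal analysis. Covariate adjustment mainly gains precision, so this is an improvement rather than a correction.

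The primary fall-rate analysis uses negative binomial regression and is untouched.

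**Conclusion.** The point holds in conditional form and for the repeatedly measured secondary outcomes only. Unless imputation or a mixed-model fit is specified, repeated measures ANOVA would exclude participants with a missing scheduled value, contrary to the intention-to-treat statement in the same section. At the planned 20% drop-out this is about 60 of 300, or 20 of 100 per sub-group, for the ten outcomes scheduled at all four visits, and possibly fewer for community ambulation and Mindstreams. The 69% and 58% figures rest on assumed rates of missed visits and on independence. Bias is plausible, not demonstrated. The change should be made because a better method is available in the same software at almost no cost.

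**What to change.** For secondary outcomes measured repeatedly, replace repeated measures ANOVA with a linear mixed model for repeated measures, fitted by likelihood to all available post-training values:

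- **Fixed effects:** arm, visit, arm-by-visit, baseline value, sub-group and centre.
- **Covariance:** unstructured. With at most three post-training visits this is 3 × 4/2 = 6 parameters.
- **Reporting:** the arm difference at each visit scheduled for that outcome, with its 95% CI.
- **No post-training value:** these participants do not contribute to the model, so state a sensitivity analysis that covers them and so addresses the intention-to-treat commitment.

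Obtaining sub-group effects from an arm-by-sub-group term in this single model is optional and not part of the error.

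The cost is one paragraph of analysis wording and slightly more modelling work; no new data are needed and SPSS can fit the model. The analysis then relies on data being missing at random, which should be stated.

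### Run as named and without imputation, the secondary RMANOVA drops everyone with a missed visit, although the plan says all randomised participants are analysed; a mixed model would keep them

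*Protocol article*

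**What the plan says.** All references are to the protocol article.

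- **Data analysis, population:** "All analysis will be conducted on an intention-to-treat principle using all randomized participants".
- **Data analysis, method:** "The secondary outcome measures will be analyzed using repeated measures analysis of variance (RMANOVA) to assess differences between groups (intervention) and across time (follow up"). The sentence reads as applying this within each participant group first and then comparing the groups.
- **Data analysis, software:** "Statistical analysis will be undertaken using SPSS version 19.0".
- **Assessment protocol:** "assessments performed 1 week pre-training, post-training, and at 1 month and 6 months post intervention". Table 1 gives most secondary outcomes all four visits. Mindstreams has no 1-month visit and community ambulation has no 6-month visit, so each has three.
- **Sample size calculation:** "we accounted for drop out rate of 20"%. For the secondary outcomes, "with 22 subjects in the intervention and control arms, we will have 90% power to detect an intervention effect" on dual-task gait speed, at a Cohen's f for ANOVA of 0.21.

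The article names no imputation, mixed model or other step for missed visits.

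**The concern.** Classical RMANOVA, as in the SPSS repeated-measures GLM procedure, deletes incomplete cases listwise. Someone seen before training, after training and at 1 month, but not at 6 months, contributes nothing to a four-visit analysis, not even the post-training result. The named method then delivers a completers' analysis where the same section announces one of everybody randomised.

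Two things are at stake. Data already collected are thrown away. And if the reasons for leaving relate to how a person is doing and differ between treadmill training with and without virtual reality, the completers in the two arms are no longer comparable by randomisation. Such a difference is plausible, since the arms differ in content and cognitive load and the participants are recurrent fallers, but the documents do not establish it.

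**Working it through.** **1. The plan's secondary power figure.** Inputs from the Sample size section: f = 0.21, 22 per arm (N = 44), stated power 90%. Inputs assumed: α = 5% (given there only for the primary calculation), m = 4 visits, sphericity, and a between-visit correlation ρ of 0.5 (not given; range 0.3 to 0.7).

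Group-by-time F test: λ = f²·N·m/(1 − ρ), df₁ = m − 1, df₂ = (N − 2)(m − 1).

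λ = 0.0441 × 44 × 4 / 0.5 = 15.5 on 3 and 126 df, so power is 91.8%, close to the stated 90%. With ρ = 0.3 it is 79%, and with ρ = 0.7 it is 99%. The figure is therefore consistent with a classical four-visit RMANOVA.

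**2. How many remain.** Carrying the 20% over to the assessment visits:

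- All participants: 0.80 × 300 = 240, so about 60 leave each four-visit analysis.
- Per participant group: 0.80 × 100 = 80, about 40 per arm.
- If a further 5% miss each of three follow-up visits (assumed): 0.80 × 0.95³ = 0.686, about 206 of 300.

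The 240 is an upper limit, because intermittent missed visits add to the loss.

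**3. Power.** Using the formula of step 1 with ρ = 0.5:

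| N analysed | λ | Power at f = 0.21 |
|---|---|---|
| 44 | 15.5 | 91.8% |
| 36 (44 less about 20%) | 12.7 | 84.7% |
| 80 (one participant group, completers) | 28.2 | above 99% |

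With 80 completers and ρ = 0.3, λ = 0.0441 × 80 × 4 / 0.7 = 20.2 and power is about 97%. At the sample actually planned, power is not the problem.

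**4. Precision under random loss.** If 20% are lost at random after the post-training visit, the post-training contrast among completers has 1/0.80 = 1.25 times the variance of the all-data contrast. Simulation at 50 per arm agrees: SE 0.199 against 0.178, and (0.199/0.178)² = 1.25. For assumed effects, group-by-time power fell from 92.8% to 87.2% (0.6 SD, 50 per arm) and from 93.7% to 89.1% (0.35 SD, 150 per arm).

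**5. Bias under differential loss.** Every setting here is assumed: four visits, common correlation 0.6, no true effect, and 20% loss after the post-training visit. Loss is random in the control arm. In the TT+VR arm it depends on a poor post-training score (logit slope 1 to 1.5 per SD).

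- The raw post-training difference among completers is off by 0.17 to 0.23 SD. Baseline shifts by 0.6 of that, so the change from baseline is off by (1 − 0.6) × 0.17 to (1 − 0.6) × 0.23, about 0.07 to 0.09 SD.
- Group-by-time false positives at a nominal 5% are about 8–11% at 150 per arm and about 6–8% at 50 per arm. The second is the size of each participant group.
- An all-data likelihood model stayed near 5% (4.7%) with no bias.
- With random loss, or the same mechanism in both arms, RMANOVA also stayed near 5%.

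**6. Cross-check with a true difference of 0.30 SD** and correlation decaying over visits (0.6 or 0.8 between adjacent visits), 20% loss per arm:

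| Loss depends on post-training score | Completers, post-training | Completers, 6 months | All data, 6 months |
|---|---|---|---|
| Not at all, or equally in both arms | 0.30 | 0.30 | 0.30 |
| In controls only | 0.23 / 0.26 | 0.34 / 0.32 | 0.30 / 0.30 |
| In opposite directions | 0.16 / 0.23 | 0.39 / 0.35 | 0.31 / 0.30 |

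The error can go either way, and it appears only when the mechanism differs by arm.

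**The case against.** A reader might infer that the population sentence and the RMANOVA sentence cannot both be obeyed. The text does not support that: RMANOVA after multiple imputation would satisfy both. The article does not mention listwise deletion or completers, and an unseen analysis plan may say how missed visits are handled. Its silence on imputation in a condensed article is not itself an error. What stands is narrower: the article does fix a method, and that method, run as named, does not deliver the stated population.

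Other limits also stand:

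- The 20% belongs to the sample size calculation for falls and carries no timing. It is used here because it is the only attrition figure given. If people leave during the six weeks of training, they contribute only a baseline and a mixed model recovers little. The 25% variance penalty assumes later loss.
- Deletion is per outcome. Missing only the 6-month visit removes nobody from the community ambulation analysis, and the Balance and mobility section describes accelerometer data only before and after training. So 240 is not the figure for every secondary outcome.
- The bias scenarios are chosen, not taken from the documents. The mixed model's good showing is partly built in, because loss was made to depend on an observed score.
- At the plan's own f of 0.21 the loss of power per participant group is immaterial.

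Reading RMANOVA loosely as a mixed model is possible, but nothing in the article points that way. The secondary power statement uses an ANOVA effect size, and step 1 is compatible with the classical test.

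**Conclusion.** The point holds in limited form. Without imputation, the named method excludes from each secondary outcome's analysis anyone missing one of its visits. That does not match the stated analysis of all randomised participants. If the 20% applies to these visits, at most about 240 of 300 remain in a four-visit analysis (about 80 of 100 per participant group).

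It would be wrong to conclude that the secondary results will be biased. Bias requires outcome-related drop-out that differs between arms. In the scenarios of step 5 it is modest, and the inflation of false positives is smaller within a participant group than in the pooled sample. Otherwise the cost is some precision and discarded data. The primary negative binomial analysis of falls is untouched. The case for change rests on a better method being available at almost no cost, not on a demonstrated failure of the trial.

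**What to change.** In Data analysis, replace RMANOVA for the secondary outcomes by a likelihood-based mixed model for repeated measures (the SPSS MIXED procedure). Use visit as a category, an arm-by-visit term and an unstructured covariance across visits. Include every randomised participant with any assessment of that outcome. Keep complete-case RMANOVA as a sensitivity analysis. If RMANOVA must stay as the main method, state that it follows multiple imputation.

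The cost is one sentence, in software the plan already uses and with no extra data. The small downside is reliance on missing-at-random, which should be stated. Estimates may also be slightly less favourable than the completers' figures if completers did better.
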